## Abstract

Background: Tobacco smoking remains one of the leading preventable causes of morbidity and mortality worldwide and is associated with cardiovascular, respiratory, oral, and psychological disorders. Although conventional smoking cessation interventions are effective, barriers related to accessibility, adherence, healthcare costs, and continuity of care frequently limit long-term success. Recent advances in technology may offer innovative opportunities to improve multidisciplinary smoking cessation pathways. Methodology: The Wear-Smile project is a non-profit, monocentric, randomized controlled trial registered in the Clinical Trial Protocol Registry and Results System (code No.: NCT07593742), designed to evaluate the effectiveness of a multidisciplinary telemedicine-based smoking cessation program assisted by wearable remote-monitoring devices. Adults who smoke combustible or heated tobacco or electronic nicotine delivery systems will be randomly allocated in a 1:1 ratio to either an experimental group receiving telemedicine-assisted rehabilitation integrated with wearable monitoring devices or a control group receiving standard in-person smoking cessation care. The intervention will include a multidisciplinary behavioral smoking cessation intervention involving cardiology, respiratory, dental, and psychology specialists. Primary outcomes will include Continuous Abstinence Rates and Point Prevalence Abstinence assessed at 6 and 12 months. Secondary outcomes will include cardiopulmonary and oral health parameters, smoking-related variables, health- and oral health-related quality of life (QoL), as well as adherence, usability, acceptability, and satisfaction with the rehabilitation program. Conclusions: The project may provide preliminary evidence regarding the potential feasibility, acceptability, and effectiveness of a multidisciplinary smoking cessation program integrating telemedicine and wearable monitoring technologies in improving abstinence outcomes, patient engagement, continuity of care, and QoL.

## 1. Introduction

The World Health Organization estimates more than 8 million deaths due to direct tobacco smoke and 1.2 million deaths due to second-hand tobacco smoke each year [1].

Tobacco smoking remains one of the leading preventable causes of morbidity and mortality worldwide and represents a major modifiable risk factor for chronic non-communicable diseases [2], including cardiovascular diseases [3], respiratory disorders [4], oral diseases [5,6], and malignant neoplasms [7].

Therefore, smoking cessation programs have a central role in public health interventions, with both short- and long-term improvements for the health of persons who formerly smoked [8].

For instance, improvements in pulmonary function may already be observed within 48 hours after smoking cessation [9]; from a psychological perspective, persons who formerly smoked for at least six weeks registered lower levels of anxiety, stress, and depression symptoms after smoking cessation [10]. Furthermore, within the first three months after quitting, improvements in respiratory performance, walking capacity, and skin appearance have been described, together with a reduction in cardiovascular risk [9]. In the long term, smoking cessation contributes to lowering the incidence of cardiovascular diseases, stroke, respiratory disorders, and malignant neoplasms. Specifically, the risk of oral squamous cell carcinoma has been reported to decrease by approximately 50% after five years of smoking abstinence, while the risk of lung cancer progressively approaches that of persons who never smoked after ten years [11,12].

In this context, different healthcare providers, such as cardiologists, pulmonologists, dentists, and psychologists, should cooperate to achieve physical, social, and psychological health and well-being in persons with nicotine dependence.

Several studies have demonstrated the effectiveness of conventional face-to-face smoking cessation interventions in supporting smoking abstinence, including physician-delivered brief advice [13]. Additional benefits have been observed with more intensive behavioral interventions, such as individual or group-based counseling programs conducted in person [14,15].

Nevertheless, intensive smoking cessation interventions are frequently associated with increased healthcare costs, greater demands on healthcare professionals’ time, and longer waiting periods for persons who smoke seeking access to cessation services [16].

In recent years, advancements in intelligent hardware, software, and big data have led to the widespread adoption of wearable remote-monitoring devices across several healthcare fields, transforming healthcare by supporting a wide range of applications for subjects of all ages and for both physiological and pathological conditions [17,18,19]. These devices are employed to monitor medical parameters, track health-related biomarkers, provide therapeutic functions and remote treatment plan adjustments, and enhance athletic and military performance [17,18,20]. For chronic disease management, wearable devices were used as continuous glucose monitors [21] or to provide real-time electrocardiograms to assist in the treatment of diabetes, cardiovascular diseases, and respiratory conditions [22].

In recent decades, various technological tools have been explored to assess smoking behavior, such as measuring expired carbon monoxide and specific biomarkers. However, these approaches have not enabled the reliable identification of smoking patterns. To address this, a portable monitoring device was developed to detect smoking events, requiring users to smoke exclusively through the device. Nonetheless, compliance issues and the device’s obtrusiveness and bulkiness often led to inaccurate data recording [23].

Taking into consideration the new opportunities offered by wearable remote-monitoring devices for the continuous tracking of health-related parameters, integrating these devices into smoking cessation programs may enhance patient monitoring and support.

Furthermore, combining wearable remote-monitoring devices with an integrated telemedicine platform may facilitate multidisciplinary management by different healthcare providers.

This integrated approach may represent a promising strategy to address smoking, a major public health issue that significantly affects the overall health and well-being of persons who smoke.

The present Wear-Smile study protocol aims to describe the design and methodology of a multidisciplinary smoking cessation program based on telemedicine and wearable remote-monitoring devices for persons who smoke combustible tobacco, non-combustible tobacco products, and other nicotine-containing products.

The Wear-Smile project was designed to investigate whether the integration of wearable monitoring technologies and a telemedicine platform into a multimodal smoking cessation pathway may improve abstinence outcomes, treatment adherence, patient engagement, and health-related outcomes compared with standard in-person smoking cessation care. Furthermore, the protocol aims to evaluate the impact of the intervention on cardiovascular, respiratory, oral health, psychological well-being, and quality of life parameters through a multi-specialistic approach.

## 2. Methodology

### 2.1. Study Design and Setting

The study protocol is designed as a non-profit, monocenter, two-parallel-group (experimental and control groups), non-blinded, controlled randomized trial in persons who smoke combustible tobacco products (conventional cigarettes), heated tobacco products (HTPs), and electronic nicotine delivery systems (ENDSs).

The study protocol adheres to the updated principles of the Declaration of Helsinki and was approved by the local Ethics Committee of Azienda Ospedaliero-Universitaria San Giovanni di Dio e Ruggi d’Aragona (protocol No. 4196/2025 approved on 30 January 2026). The study was also registered in the Clinical Trial Protocol Registry and Results System (https://register.clinicaltrials.gov/, accessed on 11 May 2026) of the United States of America (code No.: NCT07593742; link: https://clinicaltrials.gov/study/NCT07593742, accessed on 26 May 2026).

The study protocol was developed according to the Standard Protocol Items: Recommendations for Interventional Trials (SPIRITs) guidelines [24].

According to the inclusion and exclusion criteria detailed below, eligible participants who voluntarily wish to participate in a smoking cessation program (for physical, social, and/or psychological reasons) and sign a written informed consent will be recruited at the Azienda Ospedaliero-Universitaria San Giovanni di Dio e Ruggi d’Aragona di Salerno, Salerno, Italy.

Before providing the informed consent form to be signed, participants will be informed about the types of data collected within the study and the procedures implemented to ensure data anonymity and confidentiality. They will also receive contact details of the study’s designated coordinator for any queries or concerns, as well as clear instructions regarding their right to withdraw from the Wear-Smile project.

Participants will be randomly distributed equally (in a 1:1 ratio) into the experimental group (EG) and control group (CG). The random allocation sequence will be carried out by the web-based randomization service Research Randomizer (freely accessible online at: https://www.randomizer.org/, accessed on 26 May 2026) by an independent researcher not involved in participant recruitment, eligibility evaluation, or outcome assessment. Allocation concealment will be ensured using sequentially numbered, opaque, sealed envelopes prepared by the independent researcher. The envelopes will be opened sequentially only after the participant has completed the baseline assessment and has been formally enrolled in the study, thereby preventing foreknowledge of treatment allocation and minimizing selection bias.

Due to the nature of the intervention, participants and healthcare providers cannot be blinded to group allocation. Outcome measures will be collected using standardized assessment procedures to minimize assessment bias by independent researchers not involved in participant recruitment, eligibility evaluation, or randomization allocation.

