### 2.2. Study Participants

The inclusion criteria will be:Person who currently smokes ≥5 cigarettes per day [25] (conventional cigarette or equivalent in nicotine content from HTP or ENDS);Adult persons who smoke (≥18 years old);Ability and willingness to provide informed consent or presence of a legal representative who consents.

The exclusion criteria will be:Persons < 18 years old;Pregnant or breastfeeding women;Current or past use of pharmacological or behavioral smoking cessation supports [25];Concurrent dependence on alcohol or other substances of abuse (excluding nicotine) [25];Advanced neurocognitive degenerative disorders;Unstable psychiatric conditions (including active suicidal ideation, recent psychiatric hospitalization, and/or changes in psychiatric medication within the past 3 months) [26,27];Inability or refusal to provide informed consent;Inability to access the integrated telemedicine platform and/or use wearable remote-monitoring devices;Participants without access to home medical devices for monitoring cardiopulmonary parameters (blood pressure monitor and pulse oximeter), required to perform the scheduled home assessments.

No restrictions regarding gender, race, nicotine addiction, or motivation to quit smoking will be enforced.

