### 2.6. Statistical Analysis

An a priori sample size estimation was performed using G*Power software version 3.1.9.7 [36]. The calculation was based on the primary outcome (CAR), assuming a one-tailed test, a type I error (α) of 0.05, a statistical power (1−β) of 0.80, and a medium expected effect size. Based on these assumptions, the estimated sample size is 102 participants (51 per group).

The data collected will be pseudonymized (a technique that modifies and masks personal and sensitive data of a natural person to prevent direct or easy attribution to the individual) and will be used exclusively for the purposes of the Wear-Smile study project.

Statistical analyses will be performed according to the intention-to-treat (ITT) principle. Per-protocol analyses will additionally be conducted as sensitivity analyses.

The statistical analysis will be applied to analyze continuous and categorical variables, with particular attention to the handling of missing data and the analysis of both intra- and inter-subject variability.

To enhance data interpretation and understanding of distributions, graphical representations such as histograms, boxplots conditioned on the target variable, and scatter plots will be employed.

To minimize the risk of bias due to missing data, a missing data analysis will be performed to assess whether data are Missing Completely at Random (MCAR) or dependent on other variables. If missing data exceeds 5%, it will be handled using multiple imputation techniques based on appropriate statistical models, thereby reducing the risk of bias.

The adoption of these methodologies will strengthen the scientific evidence regarding the effectiveness of telerehabilitation for smoking cessation, optimize result interpretation, and provide valuable insights for future clinical implementations and public health policies.

A sensitivity analysis will be conducted to compare results between the original datasets and the imputed datasets.

Statistical analyses will be performed using SPSS version 28.0, R version 4.2, or STATA version 17.0. The level of statistical significance will be set at *p* < 0.05 for all tests, with Bonferroni correction applied for multiple comparisons to control the risk of Type I error. Effect sizes and 95% confidence intervals (95% CI) will also be reported whenever appropriate.

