Before performing inferential analyses, an Exploratory Data Analysis (EDA) will be conducted to describe the characteristics of the sample and to identify any anomalies or patterns in the data.

Continuous variables will be presented as mean and standard deviation (SD) for normally distributed data and as median and interquartile range (IQR) for non-normally distributed data. Categorical variables will be reported as frequencies and percentages. The Shapiro–Wilk test will be used to assess the normality of distributions and determine the appropriate use of parametric or non-parametric tests.

Longitudinal changes in primary and secondary outcomes over time (baseline, 6 months, and 12 months) will additionally be analyzed using mixed-effects regression models accounting for repeated measurements within participants.

Comparisons between the intervention group (telerehabilitation using the integrated telemedicine platform and wearable remote-monitoring devices) and the control group (standard multimodal behavioral-psychological treatment without telemedicine or wearable devices) will be performed using Student’s t-test for normally distributed continuous variables and the Mann–Whitney U test for non-normally distributed variables.

Within-group longitudinal comparisons across follow-up assessments will be performed using paired Student’s t-tests or Wilcoxon signed-rank tests, as appropriate according to data distribution.

Comparisons between categorical variables, including smoking cessation status (abstinent/non-abstinent), will be performed using the Chi-square test or Fisher’s exact test when appropriate.

Associations between the intervention and both primary and secondary outcomes will be explored using Pearson’s correlation coefficient for normally distributed variables and Spearman’s rank correlation coefficient for non-normally distributed variables.

To control for potential confounding factors (e.g., age, gender, comorbidities), multivariate linear regression models will be applied. In addition, multiple logistic regression will be used to identify predictors of successful smoking cessation. The dependent variable will be smoking cessation status (yes/no), and the independent variables will include type of nicotine use (combustible tobacco vs. HTP vs. ENDS), age, gender, motivation, dependence severity, and comorbidities.

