Pre-specified subgroup analyses will be performed according to the type of nicotine-containing product used (combustible tobacco cigarettes, heated tobacco products, and electronic nicotine delivery systems), dependence severity, and motivation to quit. In addition, the type of nicotine-containing product will be included as a covariate in multivariable regression models to account for its potential confounding effect on smoking cessation outcomes.

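### Product type is called a potential confounder, yet no stratification by it is described and no listed analysis clearly gives a product-adjusted treatment effect on abstinence

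*Protocol article*

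**What the plan says.** Section 2.1 sets out allocation in steps. The ratio is 1:1, and "The random allocation sequence will be carried out by the web-based randomization service Research Randomizer", run by a researcher independent of recruitment, eligibility and outcome assessment. On concealment it says: "Allocation concealment will be ensured using sequentially numbered, opaque, sealed envelopes prepared by the independent researcher". On timing: "The envelopes will be opened sequentially only after the participant has completed the baseline assessment". No stratum, block or product-specific set of envelopes is mentioned.

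Section 2.2 admits users of all three products through a common consumption threshold ("conventional cigarette or equivalent in nicotine content from HTP or ENDS") and sets no quota by product.

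Section 2.6 handles product type in three ways:
- It is a pre-specified subgroup factor, alongside dependence severity and motivation to quit.
- It is an adjustment variable: "the type of nicotine-containing product will be included as a covariate in multivariable regression models to account for its potential confounding effect on smoking cessation".
- It is an independent variable in a logistic model of cessation status, whose purpose is to identify predictors. The other variables listed are age, gender, motivation, dependence severity and comorbidities. Study arm is not listed.

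The comparison of abstinence between arms is a separate, unadjusted test: "Comparisons between categorical variables, including smoking cessation status (abstinent/non-abstinent), will be performed using the Chi-square test or Fisher’s exact test when appropriate".

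**The concern.** The plan expects product type to affect quitting, and product type is known before an envelope is opened. Even so, neither the allocation as described nor the between-arm test of abstinence takes account of it. With 102 participants and three products, the HTP and ENDS groups may be small, and small groups often split unevenly by chance.

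Two things are at stake. First, an uneven split moves the observed difference in CAR and PPA if quit rates differ between products. Second, a product subgroup may have very few participants in one arm. Covariate adjustment would deal with the first, but the only model written out for a yes/no cessation outcome does not name study arm. As listed, it estimates predictors of quitting and not the treatment effect.

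**Working it through.** **Inputs from Section 2.6.** N = 102, 51 per arm. This figure reproduces: reading the stated medium effect as a standardized difference of 0.5, a one-sided two-sample t-test at α = 0.05 with 51 per arm has power 0.806 (0.799 with 50). The figure is used here only for the arm sizes, and this point does not change it.

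**Assumed inputs.** The documents give neither the product mix nor abstinence rates by product. I take a smaller product group of m = 10 to 30 users, a quit-rate difference between products of δ = 10 to 20 points, and overall abstinence p of 15 to 25%.

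**1. How uneven can a product group be?** With no strata and 51 per arm, the number k of the m users in the experimental arm is hypergeometric (102, 51, m).

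| m | P(split 2:1 or worse) |
|---|---|
| 10 (7:3 or worse) | 0.318 |
| 15 (10:5 or worse) | 0.263 |
| 20 (14:6 or worse) | 0.079 |
| 30 (20:10 or worse) | 0.050 |

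With two smaller groups, the chance that at least one splits 2:1 or worse is 53% (10 and 10), 29% (16 and 14) or 15% (20 and 20).

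**2. How far does that move the risk difference?** The shift is |2k − m| / 51 × δ.

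- m = 10: mean |2k − m| = 2.34. The average shift is 2.34/51 × 10 = 0.46 points, or 0.92 points at δ = 20.
- m = 30: mean |2k − m| = 3.64. The average shift is 3.64/51 × 10 = 0.71 points, or 1.43 points at δ = 20.

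Over m = 10 to 30 and δ = 10 to 20, the average shift is 0.5 to 1.4 points and the 95th percentile is 1.2 to 3.1 points.

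**3. What is that beside sampling error?** SE = √(2p(1 − p)/51), which is 7.1, 7.9 and 8.6 points at p = 15, 20 and 25%.

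**4. Does the unadjusted test lose its error rate?** I used simulation under no treatment effect: 200,000 runs per scenario, assumed mixes 72/16/14 and 62/20/20, three sets of product-specific quit rates each.

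| | Unstratified | Stratified |
|---|---|---|
| One-sided type I error | 0.051 to 0.052 | 0.049 to 0.051 |
| SD of risk difference (points) | 7.9 to 8.7 | 7.8 to 8.6 |

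In matched scenarios, stratifying lowered the SD by 0.02 to 0.14 points. The mean difference was zero in every case, to within 0.04 points.

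**5. A deliberately bad draw.** Let both smaller groups split about 70:30 toward the same arm, with δ = 15. For 16 and 14 users split 11:5 and 10:4, the shift is (6 + 6)/51 × 15 = 3.5 points. For two groups of 20 split 14:6, it is (8 + 8)/51 × 15 = 4.7 points. The one-sided error conditional on such a draw is 0.11 and 0.14. This shows how far an unlucky single randomization could go; it is not what to expect.

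**6. Subgroups.** Information on a between-arm contrast is proportional to n₁n₂/(n₁ + n₂). For 10 users it is 25/10 = 2.5 when split 5:5 and 21/10 = 2.1 when split 7:3. The uneven split loses 16%, but the even split is still only ten people.

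**The case against.** A reader might infer that allocation certainly uses a single unstratified envelope series. Section 2.1 does not say so. It is silent on strata, and it condenses a full protocol that is not shown. The supportable statement is that no stratification is described.

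A reader might also infer that the unadjusted comparison is biased. Step 4 does not support that: the imbalance is due to chance, averages to zero, and is already covered by the test's error rate. A shift of 3 to 4 points needs an upper-tail imbalance together with a quit-rate gap at the upper end of the assumed range.

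Regression adjustment is a recognised alternative to stratified randomization, and the plan commits to including product type in multivariable models. In principle that answers the concern. In practice, the logistic model as listed omits study arm. The other stated confounder adjustment is linear regression, which does not suit a yes/no outcome. The mixed-effects models cover the primary outcomes but are not said to contain product type. The gap is therefore in the analysis.

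Three further objections stand:
- Product type is not unique. Dependence severity and motivation have the same subgroup status, and age, gender and comorbidities are also named as potential confounders.
- Stratification hardly helps the product subgroups, because their limit is total size (step 6).
- Permuted blocks in small strata make allocation somewhat easier to guess in a non-blinded, single-centre trial.

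**Conclusion.** The point holds as a small improvement. The plan calls product type a potential confounder, describes no stratification by it, tests abstinence without adjustment, and lists no model that clearly gives a product-adjusted treatment effect.

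The size is modest. The expected shift is about 0.5 to 1.4 points against a standard error of about 7 to 9 points, and type I error stays at about 0.05. Uneven splits are common only if a product group is small: 32% for 7:3 or worse among 10 users, but 5% for 2:1 or worse among 30. All of this rests on an assumed product mix, assumed quit-rate differences of 10 to 20 points and assumed overall abstinence of 15 to 25%. The validity of the primary comparison is not in question.

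**What to change.** **Main change.** In Section 2.6, define the between-arm analysis of CAR and PPA as a logistic regression containing study arm and product type, or a Mantel-Haenszel analysis of study arm stratified by product type. The unadjusted Chi-square or Fisher result can be kept as supportive. Product type is already to be recorded, so this costs only a few lines of text and leaves N at 102. If a product group is very small or has no quitters, the logistic model may be unstable, and the Mantel-Haenszel form is then safer.

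**Optional change.** Section 2.7 says enrolment has not started, so the independent researcher can still prepare one envelope series per product, with undisclosed varying block sizes. Each participant takes the next envelope of their stratum after baseline, and dual users are assigned by their main product at screening. The costs are slightly more handling, incomplete blocks in small strata, slightly greater predictability in an open-label trial, and arm totals that may differ from 51 and 51 by a few. If allocation is already stratified in the full protocol, Section 2.1 need only say so.
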